### Statistics

#### Sample-size calculations

Sample size was calculated based on RFS, the primary outcome of the trial. We expect an overall 3-year recurrence rate of 20% in GAS group based on previous studies (Taylor et al. 2012) [*N* = 1143, event rate of 10%, 20%, and 35% for Stage I, II, III, respectively] and Yun et al. (Yun et al. 2022) [*N* = 6012, event rate of 13%, 35%, and 60% for Stage I, II, III, respectively]). A Cox regression on the anesthesia group (TIVA group versus GAS group) with a sample size of 4845 observations achieves 80% power at a 0.05 significance level to detect a hazard ratio of 0.83 in the TIVA group compared to the GAS group. This HR corresponds to an absolute risk reduction of 3% in the TIVA group compared to the GAS group. Since the most important predictors of NSCLC survival are patient-related factors and aggravating tumor characteristics (Enlund et al. 2023), we expect only a 3% difference related to the anesthetic regimens. Although a 3% absolute difference between study groups is small, we believe it is clinically significant given the ease and low cost of the anesthetic interventions. Anticipating a 10% dropout rate, 5384 subjects should be enrolled to obtain a final sample size of 4845 subjects (in each group, 2692 subjects) (Table 2). No adjustment is made on other covariates in Cox regression, under the assumption that there is no collinearity between the anesthesia group and covariates. As no study has yet examined the effect of the TIVA group compared to the GAS group on RFS, we assumed a conservative condition for the correlation structure which leads to maximizing the estimated sample size. Although we will be conducting competitive enrollment, we expect a total of 5384 subjects to be enrolled in SMC:SNU: Other in a ratio of 4:3:3 (SMC; Samsung Medical Center, SNU; Seoul National University).

**Table 2 Tab2:** The estimated study power using two-sided log-rank tests at a significance level of 0.05 according to different assumed 3-year RFS rates at each arm

Scenario	Hazard ratio	1/hazard ratio	Risk reduction	*N*	*N***	*N* per group			
						Total	SMC	SNU	Others
1	0.65	1.54	5%	1132	1260	630	315	126	63
2	0.73	1.37	5%	1533	1704	852	427	170	85
3	0.78	1.29	5%	2010	2236	1118	559	224	111
4	0.81	1.24	5%	2374	2640	1320	660	264	132
5	0.83	1.2	2%	6460	7180	3590	1796	718	358
6	0.83	1.2	3%	4845	5384	2692	1348	538	268
7	0.83	1.2	4%	3876	4307	2154	1078	430	214
8	0.83	1.2	4%	3230	3592	1796	898	360	178
9	0.77	1.3	3%	3097	3444	1722	862	344	172
10	0.77	1.3	4%	2323	2584	1292	648	258	128
11	0.77	1.3	5%	1858	2068	1034	518	206	102
12	0.77	1.3	6%	1549	1724	862	432	172	86

Power of 80%, Alpha of 0.05, *R*^2^ = 0%, *The hazard ratio* = hazard rate in TIVA group/hazard rate in inhalational group, *The risk reduction* = recurrence rate in the inhalational group-recurrence rate in TIVA group. *Software* PASS 2022 Power Analysis and Sample Size Software (2022). NCSS, LLC. Kaysville, UT, USA, ncss.com/software/pass. *N*** The total number of subjects that should be enrolled in the study in order to obtain *N* evaluable subjects, based on the assumed dropout rate of 10%. *N per group* The number of subjects that should be enrolled in one group. SMC, SNU, and Others are the categories of participating sites

*RFS* recurrence-free survival, *SMC* Samsung Medical Center, *SNU* Seoul National University; *TIVA* total intravenous anesthesia

#### Data analysis

##### Analysis set definition

Two types of analysis sets will be used: modified intention-to-treat (mITT) and per-protocol (PP) sets. The mITT set includes all subjects allocated in the TIVA or inhalation group, except those who are found to violate any important inclusion criterion or to belong to any important exclusion criterion; who do not undergo the allocated anesthesia during the intervention; and whose primary outcome was not measured during the study. The PP set includes subjects who completed the trial in the originally allocated group except those who meet drop-out criteria. The mITT set will be used as our primary analysis set whereas the PP set will be used as an additional analysis set.

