**Fig. 1 Fig1:**
[figure not shown]
The Consolidated Standards of Reporting Trials flow diagram. TIVA; total intravenous anesthesia, GAS; inhalational anesthesia

Our inclusion criteria are (1) age 19 years old or older, (2) American Society of Anesthesiologists physical status (ASA) I‒III, (3) The Eastern Cooperative Oncology Group (ECOG) performance status 0–2, (4) Lung resection surgery (segmentectomy, lobectomy, bilobectomy, pneumonectomy; video-assisted, robot-assisted, or open) with curative intent for NSCLC (clinical Tumor, Node, Metastasis (TNM) stage I–IIIA).

Exclusion criteria will be (1) distant metastasis or malignant tumor in other organs as manifested in diagnostic tests such as CT or PET scan, and not in long-term remission according to the attending surgeon, (2) severe neurologic conditions, (3) severe hepatic disease (Child–Pugh classification C), (4) renal failure requiring renal replacement therapy, (5) history of anesthesia and/or surgery within 1 year, (6) previous surgery due to lung cancer (except diagnostic biopsies), (7) contraindications to any study medication (history of allergy, hypersensitivity reaction, or any other contraindication), (8) planned joint extrapulmonary procedure, (9) surgery under cardiopulmonary bypass or extracorporeal membrane oxygenation, (10) planned postoperative sedation, (11) pregnancy, or lactation, (12) patient refusal.

Criteria for exit (drop out) from the trial are (1) patient withdrawal and (2) surgery cancelation. A Consolidated Standards of Reporting Trials (CONSORT) flow diagram will reveal the flow of study participants (Fig. 1).

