### Randomization

A stratified block randomization with a block size of 4 will be used to allocate subjects into two intervention groups (TIVA and GAS) with a 1:1 ratio. A computer-generated assignment sequence will be stratified according to the participating site and clinical cancer stage, using a web-based automated randomization system (www.gastiva.org). This system is centralized, password-protected, and encrypted. At each participating site, random allocation will be done according to the assignment sequence before induction of anesthesia.

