### Blinding

The group designation will be blinded to the following individuals: (1) patients: patients will not be informed of the randomization assignment and will receive general anesthesia during the intervention, (2) surgeons: the anesthesia process will be initiated prior to the surgeon’s entry into the operating room. This is followed by the placement of opaque drapes that effectively prevent the surgeon from observing any details of the anesthesia technique. The opaque drapes remain in place from the induction of anesthesia throughout the entire surgical procedure, (3) attending anesthesiologists: anesthesiologists in the operating room cannot be blinded to randomization assignment but are not involved in the study enrollment or assessment of the results, (4) each site will have at least two participating investigators (main investigator and outcome assessor). The main investigator will be entering patient information into an electronic case report form (eCRF), being aware of the allocated group, and collecting intraoperative data. The outcome assessor will remain blinded to the allocated group and evaluate the postoperative outcomes. All data will be uploaded on web-based eCRF of www.gastiva.org and group allocation will be opened only when all the collected data are ready for statistical analysis.

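### The primary mITT set excludes randomised patients by anaesthetic received and by outcome availability, and no analysis of all randomised patients as allocated is planned

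*Protocol article*

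**What the plan says.** The protocol article, under Analysis set definition, names two sets and no others: "Two types of analysis sets will be used: modified intention-to-treat (mITT) and per-protocol (PP) sets". On their roles it says: "The mITT set will be used as our primary analysis set whereas the PP set will be used as an additional analysis set".

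The mITT set starts from all allocated subjects and makes three removals. The first is for eligibility: "except those who are found to violate any important inclusion criterion or to belong to any important exclusion criterion". The second and third are those "who do not undergo the allocated anesthesia during the intervention; and whose primary outcome was not measured during the study".

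The per-protocol set is defined thus: "The PP set includes subjects who completed the trial in the originally allocated group except those who meet drop-out criteria". The drop-out criteria stand under Setting and population: "Criteria for exit (drop out) from the trial are (1) patient withdrawal and (2) surgery cancelation".

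Three other places bear on this:
- **Randomization:** "random allocation will be done according to the assignment sequence before induction of anesthesia".
- **Blinding:** "anesthesiologists in the operating room cannot be blinded to randomization assignment".
- **Outcomes and Measurements:** follow-up that ends early, through loss, study end or death without recurrence, is censored at the last follow-up or at death.

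**The concern.** An intention-to-treat comparison is trustworthy because membership of each arm is settled by chance alone. Here two of the three conditions for entering the primary set are met or failed after allocation.

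**Anaesthetic received.** The anaesthesiologist who delivers the anaesthetic knows the allocation. Reasons for leaving propofol need not be the same as reasons for leaving a volatile agent, so the patients removed from the two arms need not be alike.

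**Outcome measured.** In a time-to-event analysis, a patient followed for part of the period contributes that time and is then censored. Excluding patients for an unmeasured outcome adds nothing to the censoring rule if it is read narrowly, and conflicts with that rule if it is read broadly.

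The per-protocol set cannot serve as a check, because it also keeps only patients in their allocated treatment. The target effect is small (3 percentage points, HR 0.83), so even a modest selection effect deserves attention. The article also says that a negative result would settle the debate, and that asks a lot of the primary comparison.

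**Working it through.** **1. The two sets side by side**

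| Patient | Primary mITT | PP |
|---|---|---|
| Randomised, given the other anaesthetic | removed | removed (not in the original group) |
| Surgery cancelled after randomisation | removed (no allocated anaesthesia) | removed (drop-out) |
| Outcome not measured | removed | removed in practice (trial not completed) |
| Withdraws later, some follow-up | depends on the meaning of not measured | removed |

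No planned set retains the first row.

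**2. The plan's own sample size**

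Inputs from Sample-size calculations: HR 0.83, two-sided alpha 0.05, power 80%, 20% event rate, 10% dropout.

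- Events = 4(1.960 + 0.842)² / (ln HR)². With ln HR rounded to -0.18: 4 × 7.849 / 0.0324 = 969.
- N = 969 / 0.20 = 4845.
- Enrolled = 4845 / 0.90 = 5383.3, rounded up to 5384.

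Both stated figures reproduce, so the sample-size arithmetic is not at issue.

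**3. What selective removal could do (illustration)**

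Suppose no true effect, with 20% risk in both arms and about 2422 patients per arm. A fraction e, whose risk is r, is removed from the TIVA arm only. The documents give neither e nor r; both are assumed.

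- TIVA rate after removal: p = (0.20 - e·r)/(1 - e)
- Apparent HR = ln(1 - p)/ln(0.80)
- SE of ln HR = √(1/d₁ + 1/d₀), where d₁ = 2422(1 - e)p and d₀ = 2422 × 0.20 = 484
- Type I error = P(|Z + δ| > 1.96), with δ = |ln HR|/SE

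For e = 5% and r = 30%: p = (0.20 - 0.015)/0.95 = 0.1947; HR = 0.971; d₁ = 448; SE = 0.0655; δ = 0.0298/0.0655 = 0.455; type I error 7.4%.

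| e | r | TIVA rate | Shift (points) | HR | Type I error |
|---|---|---|---|---|---|
| 2% | 30% | 19.8% | 0.2 | 0.989 | 5.4% |
| 3% | 30% | 19.7% | 0.3 | 0.983 | 5.8% |
| 5% | 30% | 19.5% | 0.5 | 0.971 | 7.4% |
| 5% | 35% | 19.2% | 0.8 | 0.956 | 10.5% |
| 8% | 30% | 19.1% | 0.9 | 0.952 | 11.6% |

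If the same number at the same risk leave both arms, the two rates stay equal and the bias is nil.

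**4. What an as-allocated analysis would cost**

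Take GAS 20% and TIVA 1 - 0.80^0.83 = 16.9%. A fraction c of each arm crosses over fully (assumed). The arm rates are then mixed in proportion, HR is the ratio of ln(1 - rate), and power = Φ(√events/2 × |ln HR| - 1.96). With 5384 patients and all events captured, events = 2692 × (0.169 + 0.200) ≈ 994. The last column uses only 4845 patients' worth of events, as if the 10% allowed for dropout contributed nothing.

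| c per arm | HR | Power, 5384 | Power, 4845 |
|---|---|---|---|
| 0% | 0.830 | 83.6% | 79.6% |
| 2% | 0.836 | 80.5% | 76.2% |
| 3% | 0.839 | 78.8% | 74.5% |
| 5% | 0.846 | 75.2% | 70.8% |
| 10% | 0.862 | 65.1% | 60.5% |

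With 5% crossover in the TIVA arm only, the HR moves from 0.83 to about 0.84.

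**The case against.** **Departures may be few.** The anaesthetic is given once, soon after allocation. Patients with a contraindication to a study drug are excluded at entry. Propofol is allowed as a co-induction agent in the GAS arm, and other medication is unrestricted, so such uses are not departures. Nothing in the article links a change of anaesthetic to recurrence risk, and because deaths without recurrence are censored, frailty alone does not raise the primary event rate. All of this stands, and it is why the size of the bias must be left open. It does not justify the exclusion: if departures are few, keeping those patients costs little.

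**A reader might infer that the rule could produce an effect as large as the one sought.** The figures do not support that. Removing 5-8% at 30-35% risk moves the rate by 0.5-0.9 points against a target of 3. An extreme assumption is needed to match the target, such as 10% removed from one arm at 50% risk: (0.20 - 0.05)/0.90 = 16.7%, HR 0.82.

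**A reader might infer that patients who die or are lost early are dropped outright.** The Outcomes and Measurements sections say that they are censored, and registry linkage and telephone contact are planned. Read with those sections, the unmeasured-outcome exclusion may cover only patients with no follow-up at all. What remains is a superfluous and ambiguous criterion.

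**A reader might infer that nothing planned could reveal the problem.** That is too strong. The CONSORT diagram, the baseline comparison and the multivariable Cox model could show uneven exclusions or adjust for part of them. None of them restores the excluded patients.

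**The eligibility exclusion is defensible** if it is judged blind to arm on pre-randomisation data. The article does not state those conditions, but an analysis plan could.

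**Conclusion.** The point holds as a fault in a stated rule. An unseen analysis plan would have to contradict this definition, not merely add detail to it. The primary set conditions on the anaesthetic received and on outcome availability, the second set does not remedy this, and no as-allocated analysis of all randomised patients is planned.

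It would go too far to say that the randomised comparison is lost. The supported statement is that randomisation no longer protects it. The documents give no rate of non-adherence and no risk for the patients concerned, so the bias could be zero or material. The type I error of about 7-12% requires one-sided removal of 5-8% of patients at 1.5 to 1.75 times the average risk. With 2-3% removed at 30% risk, it stays below 6%.

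**What to change.** Redefine the primary set as all randomised patients, analysed in the allocated arm whatever anaesthetic was given. In place of the unmeasured-outcome exclusion, censor at last contact under the existing endpoint rule. Allow removal only for surgery cancelled before induction, or for ineligibility shown from pre-randomisation data, with both judged blind to arm. Keep the present mITT and PP sets as supportive analyses, and report the number and reasons for departures by arm.

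The change is to wording in the protocol and analysis plan, with follow-up continued for patients who did not receive the allocated anaesthetic. The statistical cost is dilution. Power at 5384 stays near 80% up to about 2% crossover per arm, provided that the retained patients' events are captured, and falls further above that. The sponsor should state an expected crossover rate and check the sample size against it.

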### Outcomes

#### Primary and secondary outcomes

The primary outcome of this study is recurrence-free survival (RFS) after curative resection of NSCLC. The observed time-to-recurrence is defined as the duration from the date of surgery to the earliest date between the recurrence/metastasis date and the last follow-up date due to death from any cause, any uncontrollable factor during the study, or the end of the study.

Secondary survival outcomes are locoregional RFS (LRFS), metastasis-free survival (MFS), overall survival (OS), and cancer-specific survival (CSS). The observed time-to-events for LRFS and MFS are defined similarly to that of RFS. The observed time-to-event for OS is defined as the duration from the date of surgery to the earliest date among the date of all-cause death and the last follow-up date due to any uncontrollable factor during the study, or the end of the study. The observed time-to-event for CSS is defined as the duration from the date of surgery to the earliest date among the date of cancer-specific death, and the last follow-up date due to death from any cause other than cancer-specific death, any uncontrollable factor during the study, or the end of the study. Other secondary outcomes are postoperative complications. The postoperative complication is a composite outcome defined as any complication occurring within 7 days post-surgery or at discharge if earlier. The applicable complications are defined by the Society of Thoracic Surgeons (STS) general thoracic surgery databases (Crabtree et al. 2018), and the Clavien-Dindo classification (Wong, Oliver, and Moonesinghe 2017). The postoperative complication is a reasonable surrogate for an immediate postoperative outcome, which we believe will be similar between study groups based on Pasin et al.’s meta-analysis of short-term mortality after propofol vs. volatile anesthesia (95 studies, *n* = 9806 total patients) (Pasin et al. 2015).

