##### Other details for analyses

All baseline variables will be descriptively compared between two intervention groups using appropriate summary statistics, such as mean and standard deviation, median and quartiles, or frequency and percent, and also proper testing methods, including two-sample *t*-test or Mann–Whitney test, chi-square test, and Fisher’s exact test. All tests will be two-tailed, and the statistical significance will be declared if *p* value < 0.05. All data analyses will be performed by a statistics analytic team using SPSS software (version 27.0; IBM Corp., Armonk, NY, USA) or R software (version 4.2.2; R Foundation for Statistical Computing, Vienna, Austria) or SAS software (version 9.4; SAS Institute, Cary, NC, USA) according to a pre-established statistical analysis plan.

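### The supportive per-protocol set deletes patients who withdraw after surgery instead of censoring them, and has no explicit adherence rule

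*Protocol article*

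**What the plan says.** Under Analysis set definition, the PP set is fixed as follows: "The PP set includes subjects who completed the trial in the originally allocated group except those who meet drop-out criteria". The drop-out criteria are listed after the eligibility criteria in Setting and population: "Criteria for exit (drop out) from the trial are (1) patient withdrawal and (2) surgery cancelation". No time window is attached to withdrawal, so it can fall on any day up to the 3-year assessment.

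The modified intention-to-treat (mITT) set already leaves out, besides ineligible patients, those "who do not undergo the allocated anesthesia during the intervention; and whose primary outcome was not measured during the study". The roles of the two sets are stated: "The mITT set will be used as our primary analysis set whereas the PP set will be used as an additional analysis set".

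For the primary outcome, Primary and secondary outcomes ends observed time at the recurrence date or, failing that, at "the last follow-up date due to death from any cause, any uncontrollable factor during the study, or the end of the study". That is a censoring rule, and it keeps the recurrence-free time of a patient who leaves early.

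**The concern.** The study treatment is delivered in full on the day of surgery. Later withdrawal is therefore not a departure from treatment; it only shortens follow-up. A time-to-event analysis handles that by censoring, which the outcome definition already does. The PP definition overrides it and selects patients on something that happens after treatment.

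Two things are at stake. First, valid person-time, and possibly observed recurrences, are thrown away. If patients who recur before leaving are kept while those who leave recurrence-free are removed, the PP recurrence rates are pushed up, and the HR moves when drop-out differs between arms. Second, a PP set is normally expected to say something about adherence. Here the only adherence content is the phrase about the originally allocated group. No rule is written for a switch of agent during the operation or at a return to theatre.

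**Working it through.** **Inputs from the protocol.** GAS 3-year recurrence is 20% ("We expect an overall 3-year recurrence rate of 20% in GAS group based on previous studies"). The design statement is "a sample size of 4845 observations achieves 80% power at a 0.05 significance level to detect a hazard ratio of 0.83", tests are two-sided, allocation is 1:1, drop-out is 10%, and enrolment is 5384 (2692 per arm).

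**The plan's own figure.** Schoenfeld/Cox formula: N = (1.960 + 0.842)² / (0.25 × b² × P), with P = 0.20. With b = 0.18 (ln 1.2 rounded), events = 7.849 / 0.0081 = 969 and N = 969 / 0.20 = 4845. Then 4845 / 0.90 gives 5384. Both figures reproduce. (Unrounded ln 1.2 gives 4723 and ln 0.83 gives 4522.) The present point does not depend on this.

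**Assumptions.** Recurrence and drop-out times are exponential and independent. The whole 10% is drop-out after surgery, spread over 3 years. Patients whose recurrence came before they left are kept, and those who leave recurrence-free are deleted.

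**Formulas, per arm.** Let Λ be the 3-year cumulative recurrence hazard, M = −ln(1 − drop-out), and F = 1 − exp(−Λ − M).
- D = P(leaves before recurrence) = M / (Λ + M) × F
- E = P(recurrence before leaving) = Λ / (Λ + M) × F
- Recurrence rate after deletion = E / (1 − D)

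**10% drop-out in each arm** (M = 0.1054):
- GAS: Λ = −ln 0.80 = 0.2231 and F = 0.280, so D = 0.0898 and E = 0.1902. The rate is 0.1902 / 0.9102 = 20.9%, against 20.0%.
- TIVA: Λ = 0.83 × 0.2231 = 0.1852 and F = 0.2522, so D = 0.0914 and E = 0.1607. The rate is 0.1607 / 0.9086 = 17.7%, against 16.9%.
- Deleted: 2692 × (0.0898 + 0.0914) ≈ 488.

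**Hazard ratio** (large-sample Cox estimate, true value 0.830). Censoring returns 0.830 in every row.

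| Drop-out TIVA / GAS | HR after deletion |
|---|---|
| 10% / 10% | 0.8305 |
| 20% / 20% | 0.831 |
| 8% / 12% | 0.813 |
| 12% / 8% | 0.849 |

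The 8% and 12% figures are hypothetical; the protocol gives only 10% overall. With a true HR of 1.00, equal drop-out leaves it at 1.000. The 8%/12% and 12%/8% cases give 0.979 and 1.022.

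**Dependence on the third assumption.** Ten per cent of 5384 is 538, so about 538 − 488 = 50 patients would recur first and then withdraw, if withdrawal continued at the same rate after recurrence. The literal text deletes these too. In that case the remaining patients are simply those who would not have left within 3 years. Under independence their recurrence rates are again 20.0% and 16.9%, and the HR is undisturbed. The cost is then lost data: about 538 patients and about 50 observed recurrences. The inflation above therefore belongs to the reading in which a recurrence counts as having finished the trial.

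**The case against.** The strongest reply is that little rests on this set. PP is additional; no sample size, alpha or decision rule depends on it. Adjusted models, centre-stratified or clustered analysis and a competing-risks sensitivity analysis are also planned. This stands, and it limits the severity.

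The size is also easy to overstate. The 10% is an inflation to reach evaluable subjects, and may include cancelled operations and other patients already outside mITT, so 488 is an upper bound. At equal drop-out the HR does not move in any way that matters. Patients and outcome assessors are blinded and treatment is a single session, so a large arm difference is not the expected case. With 969 events the standard error of the log HR is about 2 / √969 = 0.064. The 8%/12% shifts, ln(0.849 / 0.83) = 0.023 and ln(0.813 / 0.83) = −0.021, are about a third of that. All this stands. Censoring is itself unbiased only if leaving is unrelated to prognosis, which is the only case modelled.

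A reader might infer three stronger things that the protocol does not support:
- **That PP adds nothing on adherence and removes only patients with incomplete follow-up.** The requirement to finish in the originally allocated group could catch a switch of agent, or a different agent at a return to theatre, where the Protocol section asks for the same anaesthetic. What is missing is an explicit rule.
- **That patients lost to follow-up are certainly deleted.** Loss is not among the two exit criteria, and trial completion is not defined. The analysis plan, not shown, may define it, and Measurements provides for record linkage, telephone contact and death registries.
- **That agreement of PP with mITT will be offered as evidence of robustness to non-adherence.** The protocol says nothing of the kind.

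What does not fall is the rule on withdrawal. It is stated, has no time limit, and conflicts with the outcome's own censoring rule.

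**Conclusion.** The point holds as a minor one. As written, the PP set removes patients who received the whole treatment and withdrew later, with all their follow-up and any earlier recurrence, where the outcome definition would censor them. It has no explicit adherence criterion beyond the allocated-group phrase.

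Its size is at most about 488 patients deleted before recurrence, with PP recurrence rates up by 0.9 points (GAS) and 0.8 points (TIVA). This rests on all of the 10% being independent post-operative drop-out and on earlier recurrences being kept. The HR is unaffected in practice unless drop-out differs by arm, for which the protocol gives no figure and no reason. It would be wrong to conclude that the trial's hazard ratio is biased: the primary analysis does not use this set.

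**What to change.** In Analysis set definition, define the PP set by eligibility and by receipt of the allocated anaesthetic at the index operation and at any return to theatre, as the Protocol section already states. Remove the completion requirement and, for withdrawals after surgery, the drop-out exclusion. State that withdrawals and losses are censored at last follow-up, with data and events up to that date kept. A matching sentence beside the drop-out criteria in Setting and population would settle the conflict.

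The cost is wording in the protocol and analysis plan, with no added patients or data. The downside is that the PP set moves closer to the mITT set, which already excludes ineligible patients and those not given the allocated anaesthesia. The remaining difference would be an explicit one on adherence.
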